### Objective and Hypothesis

The primary objective of the study is to assess the efficacy and safety of TPLA vs. TURP in treating BPH. We hypothesise that TPLA has non-inferior efficacy to TURP according to the IPSS score change at 3 months from baseline and lower incidence of post-surgery complications. Secondary endpoints, including the maximum urinary flow rate, patients' quality of Life (QoL) and post-urination residue, operation time and hospitalisation time, will also be assessed.

The secondary objective is to determine the optimal target population in patients with BPH for TPLA treatment.

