### Statistical Considerations

#### Sample Size Calculation

The sample size is calculated regarding the non-inferiority of efficacy. We assume the mean IPSS changes at 3 months from baseline in the TPLA and TURP groups are the same, the standard deviation of both groups is σ = 6, and the non-inferiority margin is Δ = 3 (10, 34, and 37). With α = 0.05 and β = 0.2, a sample size of 102 is required. Considering a drop-off rate of 10%, the overall sample size is 114.

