#### Statistical Methods

We will report our results according to the CONSORT 2010 Statement (44).

The demographic and clinical characteristics of subjects in TPLA/TURP arms will be described. The qualitative variables will be presented as absolute numbers and proportions. Quantitative variables will be presented as the means ± SD or medians and IQRs as appropriate.

The primary endpoint, the IPSS score change at 3 months from baseline, will be compared using the Mann–Whitney *U*-test or Student's *t*-test as appropriate. The safety endpoint, the incidence of complications within 3 months after surgery, will be compared using the χ^2^ test. The primary analysis will be performed on the ITT set defined as all patients who meet the eligibility criteria and undergo randomisation. Predefined subgroup analysis includes the age group, BPH severity according to the baseline IPSS score, the sites grouped by country. Missing values will be imputed with multiple imputations under the assumption of missing at random except for the safety endpoints. All statistical analyses will be performed using R (version 3.5.1).

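### The trial is framed and sized for non-inferiority with a 3-point IPSS margin, but the stated primary analysis is an ordinary two-sample comparison that does not use the margin

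*Protocol article*

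**What the plan says.** Under Objective and Hypothesis, the protocol article states: "We hypothesise that TPLA has non-inferior efficacy to TURP according to the IPSS score change at 3 months from baseline". The Abstract says the same.

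Under Sample Size Calculation: "The sample size is calculated regarding the non-inferiority of efficacy". The inputs are a common mean change ("We assume the mean IPSS changes at 3 months from baseline in the TPLA and TURP groups are the same"), a common spread ("the standard deviation of both groups is σ = 6") and a margin ("the non-inferiority margin is Δ = 3"). Then: "With α = 0.05 and β = 0.2, a sample size of 102 is required", and after allowance for loss, "Considering a drop-off rate of 10%, the overall sample size is 114". The calculation does not say whether α is one-sided or two-sided.

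Under Statistical Methods, the primary analysis is one sentence: "The primary endpoint, the IPSS score change at 3 months from baseline, will be compared using the Mann–Whitney" U-test or Student's t-test, whichever is appropriate. The next sentence uses the same form for the χ² comparison of complications, where the hypothesis is a lower incidence with TPLA, that is, a difference. Statistical Methods does not mention the margin. The margin's value appears only in the sample size paragraph.

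**The concern.** The hypothesis and the sample size ask whether TPLA is worse than TURP by less than 3 points on mean IPSS change. The named tests, in their usual form, ask whether the two groups differ at all.

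- A non-significant result is compatible with a true deficit of 3 points or more, so it does not show non-inferiority.
- A significant result in favour of TURP does not show it either.
- A significant result in favour of TPLA does, because the interval then excludes zero on the favourable side and therefore excludes a 3-point deficit. The design assumes equal means, so this is not the result it expects.
- The Mann–Whitney p-value compares ranks. It cannot be read against a 3-point margin on the difference in means, which is the quantity the trial is sized on.

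What is at stake is the primary conclusion of an open-label comparison with the standard operation. Without a stated rule that uses the margin, the criterion for success could be settled after the data are seen.

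**Working it through.** **Inputs (all from Sample Size Calculation, with 1:1 allocation from Treatment Allocation and Blindness).** Margin Δ = 3, SD σ = 6 in both groups, true difference 0, α = 0.05 (sidedness not stated), power 80%, 102 evaluable (51 per arm), 10% loss, 114 in total (57 per arm).

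**1. Reproduce the stated sample size as a test against the margin.** Normal approximation: n per arm = 2(z₁₋α + z₁₋β)²σ²/Δ².
- One-sided 0.05: 2 × (1.645 + 0.842)² × 36/9 = 49.5, so 50 per arm, 100 in total. With the non-central t distribution it is 51 per arm, 102 in total, exactly the stated figure. 102/0.9 = 113.3, so 114.
- One-sided 0.025: 126 in total (normal) or 128 (t). This does not reproduce 102.

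So the sample size was derived for a margin-based comparison of means at one-sided 0.05.

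**2. Precision.** SE = σ√(2/n) = 6 × √(2/51) = 1.188 with 51 per arm.

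**3. Where the two questions give different answers (51 per arm, 100 df, observed SD 6).**
- Non-inferiority at one-sided 0.05 needs an observed deficit below 3 − 1.660 × 1.188 = 1.03 points.
- A two-sided 5% t-test of no difference is non-significant for any observed deficit below 1.984 × 1.188 = 2.36 points.

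An observed deficit between 1.03 and 2.36 points is therefore not significantly different and yet fails non-inferiority.

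**4. Illustration: chance of a non-significant test when TPLA is truly worse by exactly 3 points (SD 6).** The standardised deficit is 3/SE = 3/1.188 = 2.53 with 51 per arm. With 57 per arm, SE = 1.124 and the standardised deficit is 2.67.

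| Test of no difference | 51 per arm | 57 per arm |
|---|---|---|
| t-test, two-sided 5% | 29.4% | 24.6% |
| Mann–Whitney, two-sided 5% (20,000 simulations, normal data) | 31.7% | 26.7% |
| t-test, one-sided 5% | 19.4% | 15.7% |

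A one-sided 5% test against the margin would claim non-inferiority in 5% of trials at this deficit.

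**5. Power of the margin-based test if the true difference is 0 (normal approximation).**

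| One-sided alpha | 51 per arm | 57 per arm |
|---|---|---|
| 0.05 | 81% | 85% |
| 0.025 | 71% | 76% |

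**The case against.** The strongest reply is that the two paragraphs sit under one heading, Statistical Considerations, and should be read together. The sample size paragraph supplies the hypothesis, margin, alpha and power. A Student's t-test can be run against a null shifted to the margin, and the stated 102 matches exactly such a test. Even an unshifted t analysis yields a mean difference and a standard error, from which a confidence bound can be set against 3. This is a condensed article, and the wording of the bound may stand in a full protocol or analysis plan that is not shown.

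Much of this stands. A margin-based t analysis may well be intended, and it would be wrong to say that the plan cannot establish non-inferiority. What does not stand is that nothing is amiss in the text itself. The article does not merely leave the test open. It names the primary tests in the form it uses for a difference hypothesis, and it allows a rank test that has no link to the margin on the mean.

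Two stronger readings are tempting and should be resisted.

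- A reader might infer that the trial has a false-claim rate of 25–29%. That figure belongs to a rule under which p > 0.05 means success, and the article states no such rule. The figure also moves with the form of test, as step 4 shows.
- A reader might extend the problem to IPSS at 6, 12 and 24 months. The article sets non-inferiority and the margin for month 3 only, lists the later times as secondary endpoints and names no test for them. The documents give no basis for a 3-point reference there.

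**Conclusion.** The concern holds as a mismatch between the stated hypothesis and the stated primary analysis. As written, only a significant result in favour of TPLA would answer the non-inferiority question. Every other result of the named tests leaves it open unless a margin-based reading is added that Statistical Methods does not contain.

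The size is best given by the range of results affected: with 51 per arm and SD 6, observed deficits from 1.03 to 2.36 points. The 29% and 25% against 5% show how far a non-significance reading would mislead at a true 3-point deficit. They rest on the protocol's SD, on the two-sided t-test, and on a success rule that the protocol does not state.

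Because this is the primary conclusion, the text should be corrected before the analysis.

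**What to change.** In Statistical Methods, replace the sentence on the primary endpoint with wording to this effect:

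- The primary analysis estimates the TPLA minus TURP difference in mean 3-month IPSS change, with positive values meaning TPLA is worse, and gives its confidence interval.
- Non-inferiority is declared only if the upper confidence bound, at a stated one-sided alpha, is below 3 points.
- A non-significant test of no difference is not evidence of non-inferiority.
- Any Mann–Whitney result is supportive only.

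The one-sided alpha must be written out in both paragraphs, because α = 0.05 without sidedness leaves the bound undefined. At one-sided 0.05 the stated 102 reproduces, with power of about 81% at 51 per arm, and no patients are added. At one-sided 0.025 power at that size is about 71%. The stated 80% would then have to be restated, or the evaluable number raised to about 126–128.

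The cost is one paragraph of wording. No data collection changes. If an unpublished analysis plan already contains such a rule, the task is only to bring the protocol text into line with it.

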This study aims to evaluate the following: the efficacy and safety of TPLA to treat BPH compared with TURP; to explore the clinical value including the prognosis and curative effect of TPLA after long-term follow-up; to seek scientific advice to optimise the relevant parameters and precautions of TPLA treatment and; to provide evidence for the indication of TPLA by analysing the advantages and disadvantages in subgroups.

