##### Inclusion Criteria

Patients with LUTS caused by BPH who have failed prior treatment or are unsuitable for medical treatment as judged by the clinician.Male older than 50 years.IPSS score ≥8.Prostate volume measured by TRUS between 30 and 100 ml.A maximum urinary flow rate (Qmax) ≤15 mL/s.Transabdominal bladder ultrasonography: post-urination residue ≥50 ml.Provide Informed consent.

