### Procedures

#### Treatment Allocation and Blindness

Confirmation of the study eligibility is required before patients are randomly assigned to receive treatment. The investigator will review the screening procedure and confirm that the patient meets all the inclusion criteria and does not meet any of the exclusion criteria. Subjects willing to randomise will be enrolled in the RCT cohort and assigned to the TURP or TPLA treatment at 1:1 randomly. Computer-generated random numbers applied. The stratified block randomisation will be applied using the Interactive Web Response System (IWRS; URL: https://jcri.shsmu.edetek.cn/actims_ngm_V2/login.action), which was designed by Clinical Research Institute of Shanghai Jiao Tong University School of Medicine (Shanghai, China). The stratification factors include study sites and severity of BPH (according to the baseline IPSS score, 8–19 as moderate, and 20–35 as severe). Study sites will conduct competitive enrolment with four as the minimum sample size requirement. Because the trial is open-label, both the patients and the surgeon are aware of the treatment allocation, but the outcome evaluations are performed by blinded readers.

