## Discussion

This study is a multicentre randomised clinical trial to assess the efficacy and safety of the novel surgery technique TPLA, which may provide an alternative treatment with lower surgery complications for properly selected BPH patients. With a relatively large sample size, this study intends to achieve internal and external validity at the same time. TRUS-guided TPLA provides a new method for patients with BPH with moderate or severe LUTS. Using very thin applicators and high-precision energy delivery, percutaneous laser ablation has been demonstrated to be safe and effective (45–48). Several preliminary studies including short-term follow-up proved its feasibility, Pacella revealed IPSS improved from 22.5 ± 5.1 to 7.7 ± 3.3 at 6 months and 7.0 ± 2.9 at 12 months, Cai HJ proved ultrasound guided TPLA effective and safe with the QoL improved from 4.9 ± 1.7 to 2.3 ± 1.3 and the Qmax improved from 8.5 ± 3.0 to 15.2 ± 4.8 mL/s at 6 months after the procedure (37, 41). However, no comparison with patients treated with other techniques has been performed, especially TURP, the most widely used surgical method and “gold standard” for BPH patients. This clinical trial will focus on comparing TPLA with TURP, evaluating the results with efficacy, safety index, and health economics assessment.

The use of TRUS guidance with a biplane probe allows repositioning of applicators during the manoeuvre based on the physician experience, and the amount of energy is planned in advance according to the baseline volume of the prostatic lobes (35, 38, 49). The assessment of the extent of the coagulation zone after ablation with transrectal contrast-enhanced ultrasonography is considered a very useful tool for early result assessment (50–52). Therefore, ultrasonography plays an important role in the study. With the monitor of real-time TRUS picture, the laser fibre could be placed precisely in the location and be adjusted dynamically. TRUS guidance contributes to reduce the possibility of urethral injury, and contrast-enhanced ultrasonography after TPLA is helpful to evaluate the dimension and evolution of coagulation, and a supplementary ablation could be conducted if necessary (53).

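### The severity subgroup cuts baseline IPSS at 19/20, which loses part of the information on effect modification that the target-population objective needs; a continuous interaction model beside the tables is a cheap improvement

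*Protocol article*

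**What the plan says.** The Objective and Hypothesis section states: "The secondary objective is to determine the optimal target population in patients with BPH for TPLA treatment". The last paragraph of the Introduction says how evidence for the indication will be obtained: "by analysing the advantages and disadvantages in subgroups".

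Statistical Methods then names the planned subgroups: "Predefined subgroup analysis includes the age group, BPH severity according to the baseline IPSS score, the sites grouped by country". Severity is defined in only one place, Treatment Allocation and Blindness, where it is a stratification factor: "severity of BPH (according to the baseline IPSS score, 8–19 as moderate, and 20–35 as severe". For age the article gives only the eligibility limit ("Male older than 50 years"), with no cut-points and no number of groups. Table 1 shows IPSS collected at screening and at every follow-up visit.

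The article describes no analysis with IPSS or age on its measured scale, and no interaction model.

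**The concern.** Two of the three subgroup factors, baseline IPSS and age, are measured on a fine scale but are to be analysed in groups. For IPSS the split at 19/20 treats scores of 8 and 19 as alike, and scores of 19 and 20 as different. It yields two estimates of the TPLA–TURP difference, which say little about how that difference moves as severity rises.

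The cut is sensible for stratifying randomisation. Nothing in the article requires it to be the only scale on which effect modification is examined. The trial is sized for the overall comparison alone, so information on interactions is scarce from the start. If the advantage of one treatment drifts gradually with baseline severity, a two-group contrast will miss it more often than a test on the full score.

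**Working it through.** **Inputs**

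- Sample Size Calculation: "the standard deviation of both groups is σ = 6, and the non-inferiority margin is Δ = 3"; "With α = 0.05 and β = 0.2, a sample size of 102 is required". Allocation is 1:1.
- Baseline IPSS: the article gives no expected distribution for this trial. The Discussion quotes a single-arm TPLA series: "IPSS improved from 22.5 ± 5.1 to 7.7 ± 3.3 at 6 months". I borrow its baseline mean of 22.5 and SD of 5.1 as an assumption and vary both.
- Eligibility and the upper end of the severe stratum limit the score to 8–35.
- The form and size of any interaction are assumptions; the article gives none.

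**The plan's own figure.** n per arm = 2(1.645 + 0.842)² × 6² / 3² = 49.5, so 50. The t-based version gives 50.15, so 51 per arm and 102 in total. Then 102 / 0.90 = 113.3, so 114. Both stated figures reproduce with one-sided α = 0.05. The 102 evaluable patients are used below.

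**Information kept by the cut.** For a linear interaction, cutting a covariate X in two keeps a share corr(X, group)² of the information. For normal X cut at standardised point c, with p the proportion below the cut, this is φ(c)² / [p(1 − p)]. The cut is placed at 19.5.

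- Mean 22.5, SD 5.1: c = −0.588, φ(c) = 0.3356, p = 0.278. Share kept = 0.1126 / 0.2008 = 0.561, a loss of 43.9%. On whole-number scores limited to 8–35 the loss is 42.5%.
- Mean 20, SD 5.1: c = −0.098, φ(c) = 0.3970, p = 0.461. Share kept = 0.1576 / 0.2485 = 0.634, a loss of 36.6%.
- Other mean/SD pairs tried (18/5.1, 19.5/5.1, 20/6, 22.5/4, 22.5/6, 22.5/7, 25/5.1): 34–59%, taking the normal and limited-range versions together. This range is not a bound; a high mean with a small SD would lose more.

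**Detectable effect** (mean 22.5, SD 5.1, residual SD 6, two-sided 5%, 80% power, normal approximation).

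- Full score: SE of the interaction slope = 2 × 6 / (√102 × 5.1) = 0.233. Detectable slope = 2.80 × 0.233 = 0.65 per baseline point.
- Cut: SE of the difference between subgroup effects = 6 × √[4/(102 × 0.278) + 4/(102 × 0.722)] = 2.65. Detectable difference = 2.80 × 2.65 = 7.4 points. The two groups' mean scores differ by 0.3356 × 5.1 / 0.2008 = 8.52 points, so this corresponds to a slope of 7.43 / 8.52 = 0.87.
- Check: (0.653 / 0.872)² = 0.56, which agrees with the share kept.

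**Power by simulation** (3,000 trials per setting, 51 per arm, residual SD 6, baseline mean 22.5 and SD 5.1 limited to 8–35, two-sided 5% test of the interaction). The two lowest slopes come from separate recalculations on the same inputs. Repeat runs agree within about 3 percentage points.

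| Slope (IPSS points per baseline point) | Full score | Cut at 19/20 |
|---|---|---|
| 0.1 | 7% | 6% |
| 0.2 | about 13% | about 10% |
| 0.3 | 23% | 16% |
| 0.4 | 37% | 23% |
| 0.6 | 67% | 44% |
| 0.7 | 81% | 56% |

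With mean 20 and SD 5.1 the pairs are 38% and 25% at slope 0.4, and 69% and 50% at 0.6.

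**If the effect is a step.** With a 6-point step at 20 and no slope, the order reverses: about 61% power for the cut and 37% for the linear model.

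**Age.** No cut is stated, so no loss follows from the document. A median split of a normal covariate loses 36%, three equal groups 21% and four 14%. Single cuts between 60 and 75 years, under assumed age distributions, lose about 35–69%.

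**What the continuous model can show.** The 95% half-width of the estimated difference at baseline score x is 1.96 × (12 / √102) × √[1 + ((x − 22.5)/5.1)²]. This gives ±6.2 at 10, ±4.1 at 15, ±2.6 at 20 and at 25, and ±4.1 at 30.

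**The case against.** The strongest reply has four parts.

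1. **The cut has a basis.** It is the randomisation stratum and carries the moderate/severe labels. Reporting by a stratum fixed in advance guards against data-driven cut-points. This stands, and is why the tables should stay.
2. **The percentage is not a feature of the plan.** It needs a normal baseline, a linear interaction and a distribution borrowed from another series. This stands; the figure is usable only with those conditions attached.
3. **The power gain is shown where effect modification is dramatic.** A slope of 0.6 moves the difference by 12 points between baseline scores of 10 and 30, four times the margin of 3. At 0.2 or below both tests have little power and the gain is a few percentage points at most. This also stands and limits the practical weight of the point.
4. **The article says the subgroup analysis includes these factors, and an analysis plan that is not shown may add a continuous model.** That is possible. The point made here is narrower: the route to a named objective that the article does state is categorical, and a better method is available on the same data.

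A reader might also infer that the continuous model would reveal the severity at which TPLA begins to fall behind. The half-widths do not support that. At scores of 10, 15 and 30 they exceed the margin, so an observed difference of zero there could not exclude a deficit of 3 points.

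**Conclusion.** The point holds as a cheap improvement; it is not an error in the plan. Under a roughly normal baseline and a linear interaction, the 8–19 against 20–35 split loses about 37–44% of the information on effect modification by baseline IPSS (mean 20 to 22.5, SD 5.1), and 34–59% over the other distributions tried. In power terms this is about 7 percentage points at a slope of 0.3, 14 at 0.4 and 23 at 0.6, and close to nothing at 0.1.

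Two stronger readings are tempting and unsupported. One is that the same percentage applies to age: without stated cuts it cannot be derived. The other is that the severity subgroup should be dropped: it matches the randomisation strata, and if the effect really changed in a step at 20 it would be the better analysis. The overall non-inferiority comparison is untouched.

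**What to change.** In Statistical Methods, keep the predefined subgroup tables and add a sentence: effect modification by baseline IPSS and by age will also be examined in linear models for 3-month IPSS with treatment, the continuous covariate and their interaction. Report the TPLA–TURP difference with its 95% CI across the observed range of each covariate. Label it exploratory and say that the intervals widen away from the mean.

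The moderate/severe table then serves as a check on linearity and would still show a step. Country remains categorical.

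The cost is two regressions on data already collected, with no added patients, visits or assessments. The downside is the linearity assumption and two more exploratory results to interpret with restraint.

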## Discussion

This study is a multicentre randomised clinical trial to assess the efficacy and safety of the novel surgery technique TPLA, which may provide an alternative treatment with lower surgery complications for properly selected BPH patients. With a relatively large sample size, this study intends to achieve internal and external validity at the same time. TRUS-guided TPLA provides a new method for patients with BPH with moderate or severe LUTS. Using very thin applicators and high-precision energy delivery, percutaneous laser ablation has been demonstrated to be safe and effective (45–48). Several preliminary studies including short-term follow-up proved its feasibility, Pacella revealed IPSS improved from 22.5 ± 5.1 to 7.7 ± 3.3 at 6 months and 7.0 ± 2.9 at 12 months, Cai HJ proved ultrasound guided TPLA effective and safe with the QoL improved from 4.9 ± 1.7 to 2.3 ± 1.3 and the Qmax improved from 8.5 ± 3.0 to 15.2 ± 4.8 mL/s at 6 months after the procedure (37, 41). However, no comparison with patients treated with other techniques has been performed, especially TURP, the most widely used surgical method and “gold standard” for BPH patients. This clinical trial will focus on comparing TPLA with TURP, evaluating the results with efficacy, safety index, and health economics assessment.

The use of TRUS guidance with a biplane probe allows repositioning of applicators during the manoeuvre based on the physician experience, and the amount of energy is planned in advance according to the baseline volume of the prostatic lobes (35, 38, 49). The assessment of the extent of the coagulation zone after ablation with transrectal contrast-enhanced ultrasonography is considered a very useful tool for early result assessment (50–52). Therefore, ultrasonography plays an important role in the study. With the monitor of real-time TRUS picture, the laser fibre could be placed precisely in the location and be adjusted dynamically. TRUS guidance contributes to reduce the possibility of urethral injury, and contrast-enhanced ultrasonography after TPLA is helpful to evaluate the dimension and evolution of coagulation, and a supplementary ablation could be conducted if necessary (53).

To the best of our knowledge, the sample size is much larger than most of the previous studies. The randomisation, standard follow-up procedure, and blinding of raters are adopted to increase internal validity. The multicentre, international cooperation are adopted to increase external validity.

TPLA provides a new method of operation, but the indication is relatively narrow compared with TURP. Patients with bladder dysfuntion (38), rectal surgery history, an oversized prostate with a prominent medial lobe or BPH with cystolith would not be appropriate for TPLA. As a matter of fact, it's an supplementary option for BPH patients, instead of a replacement to other surgery method. The procedures should be performed by very experienced interventional physicians with sufficient knowledge of US-guided thermal ablation, which could be a limitation for the technique to be generalised. Technically speaking, the skill and technique levels in each centre vary, so our experienced experts and professors would provide instruction to ensure successful TPLA proceeds before official recruitment, and a teaching video would be transmitted to investigators. Each centre is requested to successfully accomplish at least two TPLA operations independently before the official enrollment. During the procedure, the images and operation videos would be recorded and transmitted to the supervisors for quality control. Another limitation is that the IPSS and complication confirmation may be subjective; thus, our independent blind evaluators would be indispensable.

This randomised controlled multicentre clinical trial comprehensively compare the safety and efficacy of TPLA with TURP in patients with BPH, especially concerning the improvement of LUTS, the patients' QoL and complication incidence. The results of this study will help to illustrate the clinical value of TPLA and provide a beneficial alternative treatment for BPH patients.

